### **Social Functioning Scale**

The Social Functioning Scale (SFS) assesses social functioning and social participation. It consists of 78 items divided by 7 subscales: social engagement/withdrawal, interpersonal communication, independence-competence, independence-performance, recreation, pro-social behavior and employment. The SFS is reliable, valid, sensitive and responsive to change (Birchwood et al. 1990)

### **Faux Pas Task**

The Faux Pas task consists of 10 short descriptions of social situations. Participants have to answer questions about the situation, for example 'Did anyone say something he/she better shouldn't have said?' and 'Who said something he/she shouldn't have said?'. The task involves recognizing faux pas.

### **Wall of Faces task**

The Wall of faces task (Simmons et al, 2006) assesses a complex form of social cognition. In the task, 32 faces are presented which vary in angry/happy and male/female ratio. Participants respond whether there are more angry or happy faces or more male or female faces. There are ambiguous (16 of each face type) and unambiguous (6/26) trials. The task allows for investigation of brain activation associated with social cognitive processes.

### **Emotional Faces paradigm**

In the emotional faces paradigm based on Fisher et al. (2014) participants complete a gender discrimination task including blocks of individual neutral, fearful, happy and angry faces. Each trial consists of a stimulus and a fixation cross. Each block comprises 6 trials, including three to five faces trials and one to three null trials consisting of a fixation cross. This task allows for examination of basal threat-related brain response.

### **Self-Expression and Control Scale**

The Self-expression and Control scale (ZECV) measures whether participants internalize or externalize feelings of anger and to what extent they can control that anger. The ZECV consists of 40 items and participants respond by rating themselves on a scale ranging from 1 'almost never' to 4 'almost always'. The ZECV has good to high psychometric properties (van Elderen, Verkes, Arkesteijn, & Komproe, 1996).

### **Internalized Stigma of Mental Illness**

The Internalized Stigma of Mental Illness (ISMI) questionnaire is designed to measure the subjective experience of stigma, with subscales measuring alienation, stereotype endorsement, perceived discrimination, social withdrawal and stigma resistance. The questionnaire contains 29 items. The ISMI has a high internal consistency and test-retest reliability (Ritsher, Otilingham & Grajales, 2003).

### **Schaal interpersoonlijk gedrag**

The Schaal Interpersoonlijk Gedrag (SIG; W.A. Arrindell, P.M. de Groot & J.A. Walburg, 1984) measures interpersonal behaviour by means of 50 items divided over 4 subscales: expression of negative emotions, expression of positive emotions, expression of insecurity, express yourself. Respondents fill in the level of discomfort they feel and the frequency of occurrence of social situation-items on a five-point-scale. The scale has an internal consistency of  $\alpha = .80$ .

### **Self-Esteem Rating Scale – Short Form**

The original 40-item SERS was reduced to a psychometrically good 20 item version of the SERS, the SERS-SF. The 20-item Self-Esteem Rating Scale (SERS-SF) assesses self-esteem by means of a positive and negative self-esteem subscale. The two scales have excellent internal consistency ( $\alpha = .91$  positive scale;  $\alpha = .87$  negative scale). The test-retest reliability of both scales is high ( $r = 0.90$ ;  $r = 0.91$ ). The SERS total score correlated highly with both scales ( $r = 0.72$  and  $r = 0.79$ ), indicating good convergent validity (Lecomte et al. 2006).

### **Brief Negative Symptom Scale**

The Brief Negative Symptom Scale (BNSS) is a 13-item semi-structured interview, which has been developed to assess current level of negative symptoms in treatment studies. The instrument is an addition to the Positive and Negative Syndrome Scale (PANSS) and it consists of 6 subscales: anhedonia, distress, asociality, avolition, blunted affect and alogia.

### **Positive and Negative Symptom Scale**

The Positive and Negative Syndrome Scale (PANSS) is administered to monitor the changes in primary symptoms. The PANSS is a 30 item rating scale based on chart review and a semi-structured interview. It is widely used for assessing positive, negative and cognitive symptoms (Kay, Flszbein, & Opfer, 1987).

### **Manchester Short Assessment of Quality of Life**

The Manchester Short Assessment of Quality of Life (MANSA; Priebe et al., 1999) is a short version of the Lancashire Quality of Life Profile (LQLP; Oliver, 1991), and has been developed to measure quality of life of psychiatric patients. The questionnaire consists of four objective items and twelve subjective items. The objective items assess victimization and accusation of crime in the past year, whether someone has a good friend and whether the participant had contact with this friend in the past week. The subjective items assess satisfaction with life as a whole, job, financial situation, leisure activities, accommodation, personal safety, sex life, people with whom the individual lives with, relationship with family, physical health, mental health and friendships. The internal consistency is sufficient ( $\alpha = .74$ ) to good ( $\alpha = .81$ ).

### **Trauma Screening Questionnaire**

The Trauma Screening Questionnaire (TSQ) examines whether participants can be diagnosed with post-traumatic stress disorder (PTSD). The TSQ is a short screening instrument and consists of five re-experiencing and five arousal items from the DMS-IV PTSD criteria. Participants report whether or not they experienced the item twice in the past week. The sensitivity and specificity of the TSQ are high (Dekkers, Olff, & Näring, 2010).

### **Nationale Herstelschaal**

The Nationale herstelschaal (NHS) is a Dutch scale which is developed to assess personal recovery of individuals with (severe) mental illnesses. The 26 item scale consists of two subscales: personal recovery and recovery with regard to interpersonal relations. The instrument is reliable and valid (van Weeghel et al. 2015).

### **Accelerometer**

Accelerography is a valuable tool for motion analysis in psychiatry (Teicher 1995). It has been used in psychosis to study sleep and circadian rhythms (Haug et al., 2000; Hofstetter et al., 2005; Martin et al., 2005; Poyurovsky et al., 2000; Shamir et al., 2000; Wulff et al., 2006). However, data on quantitative motor activity can also be obtained using accelerometers (Farrow et al., 2005; Farrow et al., 2006; Walther et al., 2009). All subjects will wear an accurate and validated accelerometer for the continuous recording of motor activity. The accelerometer is a light and small device which can be worn at the wrist, ankle or hip.

### Modified Shuttle Test

The Modified Shuttle Test is a sub-maximal test to measure endurance. Participants have to walk between two points. A beep tells when the participant has to be at the other point. The interval between the beeps becomes shorter every beep. The MST has been studied and is appropriate for people who suffer from somatic disorders or decreased fitness (Campo, Chilingaryan, Berg, Paradis, & Mazer, 2006; Klijn, Van der Baan-Slootweg, & Van Stel, 2007).

### Simple Physical Activity Questionnaire (SIMPAQ)

The Simple Physical Activity Questionnaire contains eight questions regarding physical activity during the past seven days. The aim of including the questionnaire is to investigate its validity.

#### 6.1.3 Main study parameters/end point MRI-part

MRI is a non-invasive way to study and visualize the structure of the living human brain. This method measures the concentration of water in different tissue types, based on the magnetic resonance of protons. Functional MRI permits the visualization of brain regions activated during the performance of a specific (mental) act, in this case during the performance of a social judgement task and an facial expression task. The method is based on a change in local blood oxygen perfusion in the activated region. The measure of interest is called blood oxygenation level dependent (BOLD) signal. Due to a poor signal to noise ratio, a single measurement is insufficient. Therefore, the brain is scanned a large number of times during an fMRI scan in order to improve the signal to noise ratio. In addition to functional scans, an (T1-weighted) anatomical scan is required in order to localize functional activation.

#### 6.1.4 Covariates

To see what factors influence the results, demographic and biographic variables and substance use will be included in the assessment (Table 3). Alcohol and drugs use is measured before and after the intervention in case something changes during the treatment. Substance use is measured with the “Screening risico op verslavingsproblemen” (Spijkerman, Hendriks, van der Gaag, 2011) and consist of eleven questions regarding how much alcohol and drugs the participant uses in one week or month. Questions about gender, family contact, age, medication and residential area are only asked at baseline. .

Table 3: covariates

| Parameter         | Instrument          | Duration   | Type        |
|-------------------|---------------------|------------|-------------|
| Alcohol drugs use | Screening
Risico | 10 minutes | Self-rating |

|                                                                                 |                            |            |                                 |
|---------------------------------------------------------------------------------|----------------------------|------------|---------------------------------|
|                                                                                 | Verslavingsproblemen       |            |                                 |
| -Gender
-Family contact
-Age
-Medication
-Safety residential area * | Biographical questionnaire | 10 minutes | Open questions and rating scale |

\* based on neighbourhood crime statistics from IVM obtained from the police department.

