Before the development of the intervention we contemplated the underlying processes. Research has revealed several factors to be associated with victimization in patients with psychotic disorder. For example, alcohol and drug use (Chapple et al., 2004), homelessness (Walsh et al., 2003), perpetration (Honkonen, Henriksson, Koivisto, Stengård, & Salokangas, 2004), lack of meaningful daily activity (Fitzgerald et al., 2005), comorbid personality disorder (Dean et al., 2007), severe symptoms (Brekke, Prindle, Bae, & Long, 2001), and positive symptoms are all associated with an increased risk of victimization (Cohen, Palekar, Barker, & Ramirez, 2012). Not all of these factors can be readily addressed in one psychomotor intervention. For this reason, we developed a model in which we selected some of the important risk factors that may lead to victimization and are amendable to change (see Figure 1).

The first risk factor we would like to address is social cognition (DePrince, 2005). Compared to the general population people with a psychotic disorders have more difficulty with recognizing facial expressions (Evangeli & Broks, 2000), body language (Phillips & Seidman, 2008), and

emotional prosody (Hoekert, Kahn, Pijnenborg, & Aleman, 2007). This may complicate the judgment of risky social situations. For instance, they may not see it coming when one of their friends is going to be aggressive.

[figure not shown]

Figure 1: Victimization model

The second factor is insight, according to Ekinici & Ekinici (2013) poor insight is one of the pathways to aggression in schizophrenia. Poor insight in own psychotic symptoms may result in aggressive behavior creating dangerous situations for others as well as for themselves (Hiday, Swartz, Swanson, Borum, & Wagner, 1999). In accordance, problems in aggression regulation are associated with violent behavior in patients with a psychotic disorder (Witt, van Dorn, & Fazel, 2013). For this reason aggression regulation is the third risk factor that will be addressed. By addressing these three risk factors the intervention may improve social behavior and decrease victimization risk.

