#### **4.1 Sample size calculation**

Sample size was calculated using the computerprogram SPSS Sample Power. In order to find a medium effect size (0.50) with two-sided  $\alpha=0.05$ , power=0.80 and taking 25% drop-out into account, 60 participants per group are needed. This means a total sample size of 120 participants.

Sample size in fMRI studies is usually not determined by power analyses, but by experiences with similar protocols. Exact power calculations are difficult because of the complex 'mass univariate' nature of brain imaging data as well as the difficulty to estimate effect sizes in different regions of interest beforehand. Previous studies suggest that in general, 20 participants are necessary per group to achieve sufficient power and acceptable reliability (Monti, 2011; Thirion et al., 2007). Therefore, in the fMRI-part of the proposed study, 22 participants will be included per group.

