| Trauma Screening Questionnaire (TSQ)                |  |   | x | x | x | x | x |
| Social functioning scale (SFS)                      |  |   | x | x | x | x | x |
| Nationale herstelschaal (NHS)                       |  |   | x | x | x | x | x |
| Manchester short quality of life (MANSA)            |  |   | x | x | x | x | x |
| Biographical questionnaire                          |  |   | x |   |   |   |   |
| Accelerometer                                       |  |   | x | x |   |   |   |
| Other type of accelerometer                         |  | x |   |   |   |   |   |
| Modified Shuttle Test (MST)                         |  |   | x | x |   |   |   |
| Simple physical activity questionnaire (SIMPAQ)     |  | x | x |   |   |   |   |
| Montreal Cognitive Assessment (MoCA)                |  | x |   |   |   |   |   |
| DSM 5 vragenlijst algemene psychiatrische symptomen |  | x |   |   |   |   |   |

\* PANSS and BNSS scores obtained during selection are also used as baseline measure.

\*\* In case of participation in the MRI-substudy

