### 8.2 Analysis

The effect of the training on long term victimization (primary study parameter) and on general long term outcomes, will be investigated by means of a repeated measures fixed-effects analysis of variance (ANOVA). The effect on risk factors of victimization (second study parameter) will be tested using multilevel modelling with the pre- and posttest and follow-up on the first level and training condition on the second level (o.a. Snijders & Bosker, 2000). A model will be constructed for every dependent variable and the dependent variables will be adjusted for covariates. Statistical analysis will be conducted using the IBM SPSS Statistics package. Dummy variables will be constructed for every level and the statistical significance of the regression-effects will be tested using the T-test. The dummy-variables and their interaction will be added to the model as fixed effects. The level of significance is set at  $p < 0.05$ , two-sided.

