## **8.6 Benefits and risks assessment, group relatedness**

More than half of the patients with a psychotic disorder will be a victim of crime once in their live. Once being a victim the chances are high that it will happen again. Victimization can have a major impact on the lives of people with a psychotic disorder. It may worsen the psychiatric symptoms and clinical course of the patients. We expect that the psychomotor assertiveness training will prevent (re)victimization of people with a psychotic disorder and will increase social participation. Questionnaires during the assessments may be confronting or tiring. Possible risks of participation in the treatment condition may be minor muscle pain or bruises, despite the use of protection. With regard to the MRI substudy, participants may experience the noise from the scanner as unpleasant.

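### The covariates listed in the protocol leave out baseline positive symptoms and own aggression, and do not list prior victimization, although the protocol names all three as linked to victimization and measures them before training; this costs precision, not validity

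*Protocol*

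**What the plan says.** **Covariates.** Protocol section 6.1.4 states that "demographic and biographic variables and substance use will be included in the assessment". Its table lists alcohol and drug use, gender, family contact, age, medication and safety of the residential area. Section 6.2 commits to correcting for the randomisation factors: site, gender and participation in the fMRI substudy.

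**Analysis.** Section 8.2 analyses long-term victimization, the primary parameter, by repeated measures ANOVA, and the risk factors by multilevel models. After describing the latter it adds: "A model will be constructed for every dependent variable and the dependent variables will be adjusted for covariates". Whether that sentence also governs the primary ANOVA is not clear.

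**Known predictors.** Chapter 1 gives a list that includes alcohol and drug use, perpetration and severe symptoms, and ends by saying that "positive symptoms are all associated with an increased risk of victimization". It also makes aggression regulation one of the targeted risk factors. On earlier victimization, section 8.6 says: "Once being a victim the chances are high that it will happen again". The rationale in the Summary makes the same point.

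**What is measured before training.** Table 5 in section 6.3 places the PANSS at selection, with the note that "PANSS and BNSS scores obtained during selection are also used as baseline measure". It places the IVM, CTS2 and MANSA at pre-assessment. Section 6.1.2 describes CTS2 items on the respondent's own behaviour. Of the MANSA it says: "The objective items assess victimization and accusation of crime in the past year". The IVM description in the same section gives recall windows of five years at baseline, six months at the post assessments and one year at follow-up.

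**The concern.** Adjusting for a baseline variable helps to the extent that it predicts the outcome. Of the predictors that chapter 1 names, the covariate table carries only substance use. Positive symptoms and own aggression or perpetration appear neither there nor among the randomisation factors, although their baseline values will already be in the database.

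Prior victimization is the third case and is less clear-cut. It is not a listed covariate. If it enters at all, it does so as the pretest level of the repeated measures ANOVA, where a five-year recall is set against six-month or one-year recalls.

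At stake is the width of the confidence interval for the primary comparison in a trial of 120 with 25% drop-out expected. With so few evaluable participants, prognostic information that is collected but left unused is worth recovering.

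**Working it through.** **1. Inputs.** Section 4.1 (sample size) assumes a "medium effect size (0.50) with two-sided" α of 0.05, power 0.80, 25% drop-out and 60 per group. Evaluable per arm: 60 × 0.75 = 45, or 90 in total. The SD is set to 1. The protocol gives no R² or baseline-outcome correlation, so both are assumptions and are shown as ranges.

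**2. The plan's own figure.** A two-sample t-test with these inputs needs 64 per arm (63 by the normal approximation). Allowing for 25% drop-out gives 64 / 0.75 = 86, or 64 × 1.25 = 80 by the cruder inflation. Neither is 60. That is a separate matter and does not support the present point. It matters here only because the starting power at 45 per arm is 0.65 and not 0.80.

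**3. Gain from added covariates.** If covariates explain a further share R² of outcome variance, the residual SD is √(1 − R²) and the effective standardised difference is 0.50 / √(1 − R²). Two-sided t-test power at 45 per arm:

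| Added R² | Effective d | Power |
|---|---|---|
| 0 | 0.500 | 0.65 |
| 0.05 | 0.513 | 0.67 |
| 0.10 | 0.527 | 0.70 |
| 0.20 | 0.559 | 0.75 |
| 0.25 | 0.577 | 0.77 |
| 0.30 | 0.598 | 0.80 |

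The R² that counts is the share explained beyond what substance use, area safety, the randomisation factors and any pretest level already explain.

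**4. Baseline as an outcome level or as a covariate.** Take one pre/post contrast with correlation r and equal variances. The change contrast has variance factor 2(1 − r); covariate adjustment has 1 − r². The difference is 2(1 − r) − (1 − r²) = (1 − r)², which is positive for every r below 1. For r below 0.5, 2(1 − r) exceeds 1, so the change contrast is then less precise than ignoring baseline altogether. Power at 45 per arm, d = 0.50:

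| r | Baseline as covariate | Pre/post change |
|---|---|---|
| 0.1 | 0.65 | 0.42 |
| 0.3 | 0.69 | 0.51 |
| 0.5 | 0.77 | 0.65 |
| 0.7 | 0.91 | 0.86 |

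Equal variances are doubtful when the baseline window is five years and the later windows are six months or one year, so the second table shows the direction and rough size only.

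**5. The three baseline values side by side.**

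| Predictor | Named in | Measured before training | Listed as covariate |
|---|---|---|---|
| Positive symptoms | Chapter 1 | PANSS, selection | No |
| Own aggression / perpetration | Chapter 1 | CTS2 own-behaviour items, pre-assessment | No |
| Prior victimization | Summary, 8.6 | IVM, CTS2, MANSA, pre-assessment | No; possibly a pretest level |

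**The case against.** The strongest reply is that section 6.1.4 describes what will be assessed and is not a model specification, that the sentence on adjustment in 8.2 follows the risk-factor models, and that a final covariate list may sit in a statistical analysis plan that is not shown. This has force: the protocol cannot be said to have closed the list. It does, however, name a set under the heading of covariates, and that set does not follow its own account of the predictors.

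Second, prior victimization is probably not ignored. The design has a pretest and both primary instruments are given there, so a repeated measures ANOVA would ordinarily carry it as a time level. This stands. What remains is the unequal recall window and the lower precision of that route. For positive symptoms and own aggression the omission is plain.

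Third, the listed covariates are not idle. Substance use is a named predictor, and area safety drawn from neighbourhood crime statistics is plausibly prognostic. The gain from additions must be counted on top of these, so the R² range may be generous. The power formulas also treat the outcome as continuous, while the protocol describes incidents as low in prevalence.

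Two stronger readings are tempting. A reader might infer that chance imbalance on prior victimization biases the result. Randomisation and valid standard errors already allow for it. A reader might also take the MANSA item as a like-for-like baseline for the IVM because it asks about one year. It is a single objective item whose wording and scope the protocol does not give, while the IVM is a crime survey; a shared window does not make them the same measure.

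**Conclusion.** The point holds as an inexpensive gain in precision. It is not an error that invalidates the analysis. Positive symptoms and own aggression are named as linked to victimization, measured before training and absent from both lists. Prior victimization is not a listed covariate and, if used as a pretest level, enters in a less efficient form and on a different recall window.

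On the protocol's d of 0.50 with 45 evaluable per arm, power would rise from 0.65 to about 0.67, 0.70 or 0.77 for an added R² of 0.05, 0.10 or 0.25. These R² values are assumptions, and the gain shrinks to the extent that planned covariates already explain the same variance. It also need not carry over unchanged to a sparse or binary victimization outcome.

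The protocol does not support saying that these values are measured before allocation: it shows that pretests precede training but does not state when randomisation takes place.

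**What to change.** In sections 6.1.4 and 8.2, prespecify for the victimization analysis, as covariates and not as an outcome level:

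- a baseline victimization measure; the MANSA past-year item at pre-assessment is the only one described with a one-year window, with the limits noted above;
- the PANSS positive score from selection;
- the CTS2 own-aggression score at pre-assessment, with its recall period stated, since the protocol does not give it;
- the randomisation factors and baseline substance use, as already planned.

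State in 8.2 that this list applies to the primary analysis, and settle it before outcome data are seen so that the choice cannot depend on results.

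The cost is a short change of text and one degree of freedom for each of the three added terms, against about 90 evaluable participants. No new instrument, visit or participant is needed. Dropping family contact or medication from the model, or using the MANSA item at later waves as a same-window check, is optional and not part of this point.
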